##### Materials

Members of our project staff will develop a short visual presentation to be used as a guideline for videoconference recruitment, along with a parallel set of core written or verbal statements reflecting the content of the presentation in cases where only telephone calls are possible. Drawing lessons from our previous successful agency and organization recruitment experiences [46-49], both the presentation and written statements will cover a limited list of important concepts that need to be imparted (eg, “Participating in this project will require very little time from your agency – we are only asking you to send out one push message each month.”). While moving through these concepts, we will allow conversation to flow freely (eg, semistructured messaging) and also use live documentation of key concepts to ensure message fidelity.

The tangible documentation will consist of digital flyers based on the open-source marketing tools developed by the PulsePoint Foundation for general community agency recruitment, including the use of similar graphical assets and fonts. However, flyers will be differentiated sufficiently from the default *PulsePoint* flyers to make it clear that the organization itself is not conducting this project (eg, we will not use the *PulsePoint* logo). For reference, *PulsePoint*-branded recruitment flyers can be viewed by clicking on the hyperlink provided in the associated reference [50]. As community agencies have already committed to offering standard *PulsePoint* services, we expect that distributing these modified documents to agencies will be a high-leverage recruitment approach. Key messaging will be drawn from local demonstration projects by the study team (eg, “Be a Lifesaver” and “Citizen Opioid Responders”) [51] as well as general marketing and recruitment principles.

As supplemental recruitment content, exemplar videos will be drawn from work produced by the Dearborn County Health Department in Lawrenceburg, Indiana, in collaboration with the study authors to create awareness of this type of initiative and will be included as web links to YouTube versions of the videos [51].

##### After Recruitment

When communities agree to participate, they will be asked to sign an MOU regarding their participation and to respond to a small set of readiness and implementation items, such as whether the organization is already involved in naloxone distribution and whether there are local laws pertaining to opioid overdose reversal. This information will be used to locally tailor piped text into messages used for H2 (layperson recruitment).

#### Intervention (Recruitment) Arm 2

The recruitment procedures for arm 2 will be similar to those outlined for arm 1. The primary difference will be that the messaging in arm 2 will proactively address several misperceptions or stigmatizing ideas about overdose and naloxone that our recent research has suggested may be prevalent [39]. In particular, content in the fact sheets and scripts for recruitment used in arm 2 will address and preempt the following scientifically unsupported ideas (potentially among others):

“Naloxone causes risk compensation or presents a moral hazard”: it is fairly well established that OEND is not associated with increased opioid use [52-55], nor is it associated with reduced risk perceptions for heroin use [56].“Repeated overdoses are inevitable and people who experience nonfatal overdoses will die of an overdose in the near future”: while individuals who nonfatally overdose are at meaningfully increased risk, especially if they do not matriculate into a cascade of care, the substantive majority will not overdose again in the near future, and even fewer will die of a fatal overdose in the near future [57-60].“Individuals can get high from naloxone”: while this is not possible [6], our study found that 14.2% of our nationally-representative sample still believed this claim [39] to some extent.

Though brief, our debunking content will follow specific procedures that recent research (particularly around COVID-19 misinformation and vaccine hesitancy) has found to improve the efficacy of debunking messaging. These include ensuring the credibility of the source of the factual correction [61] and including a sufficient level of detail and explanation for *why* the facts are correct and the misperceptions are not [62]. This level of detail will vary in extensiveness depending on the format of a given piece of communication. The use of such short-format corrections does not seem to result in a backfire effect [63]; for example, a statement made in the arm 1 recruitment flyer (standard) might be, “Overdoses involving opioids are a public health emergency in the United States (US). The US Surgeon General recommends: ‘Be Prepared. Get Naloxone. Save a Life.’” The permutation for the arm 2 recruitment fact sheet (modified), in parallel, would be, “Rapid use of naloxone (Narcan) nasal spray is often an overdose victim’s best chance for survival. Studies show that opioid use in a community does not increase when naloxone is widely available.”

#### Inert Arm for H1 (Arm 3)

Arm 3 recruitment will mirror recruitment for arm 1, except that the stated goal for the agencies will be only to ask layperson respondents to indicate at 3 different time points whether they have attended OEND programming or carry naloxone (eg, no encouragement or messaging campaign will occur in this arm). This arm will not be actively analyzed when we test H1.

#### Outcome Variables and Measurement

In H1, we hypothesize that more community first responder agencies will agree to participate in the *PulsePoint-OD* program when contacted using procedures in arm 2 (tailored messaging) compared to procedures in arm 1 (standard messaging) within 6 and 12 months of initial contact. Our primary outcome to test this hypothesis will be the number of agencies that agree to participate in the project as a percentage of the number of agencies with which we have been able to identify appropriate points of contact for recruitment. This metric *M* will be computed as follows:

Each agency from the initial PulsePoint Foundation list that is randomized to participate in the study will be given a value *A* that is set at *0*, which indicates that we have not yet identified the appropriate point of contact at the agency.When we have identified a point of contact who can discuss *PulsePoint*, we will set the value for *A* at *1*.To define when a community first responder agency has agreed to participate, each agency will be assigned an ordinal value *R* ranging from *0* to *2*, where *0* will indicate nonparticipation or refusal, *1* will indicate that there is an agreement in principle to participate but that no formal MOU has been established, and *2* will indicate that a formal MOU has been put into place between the agency and the study team. For the purposes of hypothesis testing, we will aggregate values of *1* and *2*, but the data will be documented in ordinal form so that we can identify whether there is a concern with agencies failing to enter the MOU stage after agreeing in principle to participate.Next, the agency recruitment metric *M* for each arm will be the ratio of recruited agencies to total agencies with which active communication has been established: *M*=(*R_R>0_*/*A_A>0_*).

In addition to computation of the primary outcome metric, recruitment activities will be documented in a shared internal database, which will track, at a minimum, the nature, date, and outcome of each instance of correspondence with each community to inform our understanding of the uptake of *PulsePoint-OD* among *PulsePoint* communities and support ongoing mitigation of any issues with recruitment. Using this documentation, we will be able to estimate several secondary descriptive outcomes:

An estimate of the dose-response uptake of the intervention (eg, mean number and types of correspondence associated with agreement to participate and completion of an MOU)An estimate of the average length of time between initial contact and agreement to participate

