Agencies will be randomly assigned to a study arm using stratified allocation, with a 1:1:1 allocation ratio. Specifically, one-third of the rural agencies will be randomly assigned to each study arm, and separately, one-third of the nonrural agencies will be randomly assigned to each study arm. We will determine rural status using the definition from the US Office of Management and Budget (zip codes within metropolitan areas with an urban core of ≥50,000 people are not rural, and all other areas are rural [44]). In cases where agencies hold *PulsePoint* contracts that cover both rural and nonrural areas, we will assign a status based on the location of the numeric majority of the population in the area. Arm assignment will be according to sequential numbers (from the simple random sample; therefore, this allocation approach is also by definition random) within each stratum (eg, if there are 60 rural agencies, the 20 rural agencies with the lowest random numbers will be assigned to arm 1). This procedure will ensure allocation concealment from the rest of the investigative team until the moment of assignment. Agencies will not be informed that they have been assigned to a specific trial arm; they will simply be contacted using the procedures developed for that arm. Thus, this can be considered a blinded trial.

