##### Overview

The minimum goal of agency recruitment is to reach a memorandum of understanding (MOU) with agencies in which they agree to encourage their layperson *PulsePoint* responders to attend OEND programming and to carry naloxone (arms 1 and 2) and to indicate whether they have done so (arms 1, 2, and 3; Figure 2). The agencies will be asked to accomplish this using push messages prepared by our team and sent out by the agencies; the specific nature of these agency activities is outlined in the *H2: Layperson Responders* section.

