##### Approaches

To be replicable at scale, recruitment will be conducted using a combination of video or telephone correspondence (preferably Zoom [Zoom Video Communications, Inc], but telephone where necessary), web links, and emails containing tangible materials. A full recruitment attempt with fidelity to our model will consist of providing emailed materials and web links and attempting between 6 and 10 telephone contacts over approximately 6 months, based on best practice telephone recommendations from the American Association for Public Opinion Research [45]. Recruitment efforts will stop in the event that (1) an agency agrees to participate in the project, (2) an agency asks not to be contacted about the project again, (3) the aforementioned recruitment approaches clearly seem unlikely to yield a change in disposition, or (4) the recruitment timeline ends without the agency making a decision.

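### H1 counts an undefined agreement in principle as success alongside a signed MOU, recruiters know the arm and may stop on judgement, and the blinding claim holds only for agencies

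*Protocol article*

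**What the plan says.** All places are in the Protocol article.

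- **Outcome (H1, Outcome Variables and Measurement).** R = 1 "will indicate that there is an agreement in principle to participate but that no formal MOU has been established"; R = 2 "will indicate that a formal MOU has been put into place between the agency and the study team". The rule for the test is: "For the purposes of hypothesis testing, we will aggregate values of" 1 and 2. The metric M divides the agencies with R > 0 by those for which a suitable contact was found. R is kept in ordinal form to show whether agencies stall before the MOU, but no MOU-only test is stated.
- **Goal (Intervention (Recruitment) Arm 1, Overview).** "The minimum goal of agency recruitment is to reach a memorandum of understanding (MOU) with agencies".
- **Gate to H2 (Conceptualizing Recruitment for Layperson Responders).** The baseline push message goes out only after an MOU exists.
- **Effort (Approaches).** A full attempt has 6 to 10 telephone contacts over about 6 months. One of four reasons to stop is that "the aforementioned recruitment approaches clearly seem unlikely to yield a change in disposition".
- **Delivery (Materials; Intervention (Recruitment) Arm 2).** Recruiters hold semistructured conversations, and the arm 2 scripts differ from those of arm 1.
- **Blinding (Participants, Eligibility, and Assignment).** Allocation is concealed from the investigative team until assignment, and agencies are not told their arm. The section concludes: "Thus, this can be considered a blinded trial".

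**The concern.** The tested outcome sits one step below the protocol's own minimum goal. An agency left at R = 1 counts as an H1 success but sends no messages and gives no H2 data.

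That extra step is also the soft part of the outcome. A signed MOU is a document. An agreement in principle is a reading of a conversation, and the article gives no rule for when a friendly reply becomes a yes. The person in that conversation knows the arm, and H1 is directional in favour of arm 2.

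The number of attempts and the decision to give up are discretionary too. More persistence or a more generous reading in one arm would appear as an effect of the message. An unqualified statement that the trial is blinded would lead a reader to think this route is closed.

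**Working it through.** **Inputs.** From H1: Sample Size, Power, and Analysis: 60 agencies per arm, 30% (18/60) against 55% (33/60), two-sided alpha 0.05, 80% power. The planned analysis is a logistic regression with covariates; an unadjusted pooled z-test stands in for it here.

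**1. The plan's own figure.** With p1 = 0.30, p2 = 0.55 and mean p = 0.425:

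Power = Φ{[|p2 − p1|·√n − 1.96·√(2p(1 − p))] / √(p1(1 − p1) + p2(1 − p2))}

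= Φ{[0.25 × 7.746 − 1.96 × 0.699] / 0.676} = Φ(0.837) = 0.799.

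Exact binomial enumeration of the same test gives 0.806. The stated 80% is reproduced, so the sample size is not at fault.

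**2. How many codings decide the test.** With 18/60 in arm 1 and b/60 in arm 2, z = [(b − 18)/60] / √(p(1 − p)·2/60), where p = (18 + b)/120.

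| Arm 2 | Difference | z | p-value |
|---|---|---|---|
| 33/60 | 0.250 | 2.77 | 0.006 |
| 29/60 | 0.183 | 2.06 | 0.040 |
| 28/60 | 0.167 | 1.88 | 0.060 |

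Recoding five of the planned 33 successes (33 − 28 = 5) removes significance. Near the boundary a single agency does so. Fisher's exact test moves the boundary by one agency (30/60: p = 0.040; 29/60: p = 0.061). Each coding shifts an arm by 1/60 = 1.7 points, and by more if some agencies have no identified contact and leave the denominator.

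**3. Effect of lenient coding when the arms do not differ.** Assume a true rate of 30% in both arms, and assume that a share f of the 42 non-agreeing arm 2 agencies is coded R = 1. The arm 2 rate becomes 0.30 + 0.70f. Exact enumeration gives:

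| f (assumed) | Agencies recoded (42 × f) | Chance of a significant result favouring arm 2 |
|---|---|---|
| 0 | 0 | 2.6% |
| 5% | 2.1 | about 6% |
| 10% | 4.2 | 12.7% |
| 15% | 6.3 | 22.5% |

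**4. Cost of making the MOU the primary outcome.** The article does not give the share of agreeing agencies that sign. Assuming the same share in both arms, with the formula of step 1:

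| Share signing (assumed) | Rates | Power at 60 per arm | Needed per arm for 80% |
|---|---|---|---|
| 90% | 27.0% vs 49.5% | 72% | 73 |
| 80% | 24.0% vs 44.0% | 64% | 87 |
| 70% | 21.0% vs 38.5% | 56% | 106 |
| 50% | 15.0% vs 27.5% | 39% | 167 |

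**The case against.** The strongest reply is that nothing here is hidden. The pooling is prespecified and fits H1, whose outcome is framed as agencies that agree to participate. The authors foresaw drop-off before the MOU and keep the ordinal data to see it. The MOU is described as an operational goal and a gate for H2, not as the H1 endpoint. That stands, and it is why the pooled outcome can remain primary.

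Four stronger readings are tempting but not supported:

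- **That the recruiters themselves code R.** No coder is named, and an article may leave this to a fuller document. What is established is that recruiters know the arm and that no masked coding is stated.
- **That the blinding claim is simply false.** Agencies are not told their arm, so blinding holds on that side. The label is unqualified rather than untrue.
- **That effort ends at agreement and the MOU is not pursued.** The After Recruitment section asks agreeing agencies to sign one.
- **That discretion in stopping will differ by arm.** Nothing shows that it will. The arms share similar procedures, and 6 to 10 contacts already bounds the effort.

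The plan also promises a cautious reading of p-values, which softens the threshold argument. It does not protect the estimate: five codings are 5/60 = 8.3 points of a planned 25-point difference.

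**Conclusion.** The point holds as a badly fixed endpoint and an overstated property, not as an internal contradiction. H1 success includes a category with no written criterion, below the stated minimum goal. Recruiters necessarily know the arm and have discretion over effort, and no MOU-only test is specified as a check.

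The size is a handful of agencies: five on the planning figures, and one near the boundary. This rests on the plan's 30% rate in arm 1, 60 agencies per arm in the denominator, and an unadjusted test in place of the covariate-adjusted logistic regression. The shares of lenient coding and of signing are assumptions, shown over a range.

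A reader might infer that R = 2 should replace the primary outcome. The documents do not compel this, and at the fixed sample size the power cost is substantial unless nearly all agreeing agencies sign.

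**What to change.** 1. Keep R ≥ 1 as the primary H1 success. Prespecify an MOU-only (R = 2) analysis at 6 and 12 months as a key sensitivity analysis, reported beside the primary result with the 0/1/2 distribution by arm.
2. Define R = 1 by a written criterion, for example a written or emailed agreement. Have R coded from the contact log with the arm masked where possible.
3. Replace the judgement-based stop reason with the same fixed number of contact attempts in arms 1 and 2, and report attempts by arm.
4. Reword the blinding statement to say that agencies are unaware of their arm and recruiters are not blinded.

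The cost is a few more calls to agencies that seem unlikely to join, and a little more analysis. R is already to be recorded in ordinal form and correspondence is already to be logged, so most of this is a change of text. The Results section states that no recruitment or data collection had begun when the protocol was submitted.

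### The contact count and the time to agreement are averages tied to agreement, while contact stops because of the agency's response; neither shows whether further contacts help or how fast agencies are recruited (minor)

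*Protocol article*

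**What the plan says.** In the protocol article, Methods, H1, Outcome Variables and Measurement, the team keeps a database recording at least "the nature, date, and outcome of each instance of correspondence with each community". From it, "we will be able to estimate several secondary descriptive outcomes". Two are listed. The first is an estimate of the dose-response uptake of the intervention, with one example: the "mean number and types of correspondence associated with agreement to participate and completion of an MOU". The second is "An estimate of the average length of time between initial contact and agreement to participate".

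The Approaches section defines a full recruitment attempt as emailed materials and web links plus "attempting between 6 and 10 telephone contacts over approximately 6 months". It then gives four reasons to stop: "Recruitment efforts will stop in the event that (1) an agency agrees to participate in the project"; "an agency asks not to be contacted about the project again"; a judgement by staff that the approaches will not alter the agency's position; or "the recruitment timeline ends without the agency making a decision".

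The comparison of arms 1 and 2 rests on the primary metric M (agencies agreeing, out of agencies with an identified point of contact), tested at 6 and 12 months. The H1 sample size section illustrates it with 30% against 55% recruited. No between-arm test of the two secondary outcomes is stated.

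**The concern.** A dose-response statement needs a dose that is not itself set by the response. Here the number of contacts is cut short by the agency's answer, whether yes or no, and runs on only while there is no answer. An average of that count among agencies that agreed reports how early they happened to agree. It does not say whether a seventh or eighth call is worth making.

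The average time to agreement has a related defect. It has no value for an agency that never agrees, and the fourth stopping reason shows that the team expects some agencies to be undecided at the end. The average omits them, cannot exceed the length of the window, and carries little information on how quickly a given set of agencies is won over.

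At stake is a planning question. The Discussion treats feasibility as a consideration separate from significance testing and wants to learn how to structure recruitment for a larger study. How many contacts to budget, and how long to allow, are questions that M does not answer.

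**Working it through.** **The plan's own figure.** 60 agencies per arm, 30% against 55%, two-sided alpha 0.05. The pooled proportion is 0.425, so z = [0.25 × √60 − 1.96 × √(2 × 0.425 × 0.575)] / √(0.30 × 0.70 + 0.55 × 0.45) = (1.936 − 1.370) / 0.676 = 0.84. Power is 79.9%, so the stated 80% reproduces. The document gives no figure for the two secondary outcomes. The models below are assumptions used to show how the averages behave.

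**Contact count, no refusals.** Let each contact have the same chance h of agreement, with at most K contacts. Then P(agree) = 1 − (1 − h)^K, and the mean number of contacts among agreeing agencies is 1/h − K(1 − h)^K / [1 − (1 − h)^K].

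- h = 0.08, K = 10: P(agree) = 1 − 0.92^10 = 0.566; mean = 12.5 − 10 × 0.434/0.566 = 4.8. Every non-agreeing agency has 10.
- Set to the plan's 30% and 55% with K = 10 (h = 0.035 and 0.077): means 5.2 and 4.8, against 10.
- The same with K = 6 (h = 0.058 and 0.125): means 3.3 and 3.1, against 6.

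Every contact is equally productive by construction, yet non-agreeing agencies have more contacts.

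**Contact count, with refusals.** The protocol also stops at refusal, so let an agency that has not agreed refuse with chance r at each contact (h = 0.035, K = 10).

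| r | Mean contacts, agreeing | Mean contacts, non-agreeing |
|---|---|---|
| 0 | 5.2 | 10.0 |
| 0.05 | 4.8 | 7.7 |
| 0.10 | 4.4 | 6.1 |
| 0.20 | 3.6 | 4.1 |
| 0.30 | 2.9 | 3.0 |

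The gap closes as refusals become more frequent, and it can reverse when they come early. If 70% of non-agreeing agencies refuse at contact 1 and 30% reach contact 6, they average 0.7 × 1 + 0.3 × 6 = 2.5. That is below the 3.1 to 3.3 found above for agreeing agencies with K = 6, if that mean is kept. The sign depends on when refusals occur, not on whether further contacts work.

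**Time to agreement.** Assume constant rates that reach p by T = 6 months: λ = −ln(1 − p)/T. The mean time among agreeing agencies is 1/λ − T(1 − p)/p.

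- Arm 1: λ = 0.3567/6 = 0.0594 per month; mean = 16.82 − 6 × 0.70/0.30 = 2.82 months.
- Arm 2: λ = 0.7985/6 = 0.1331 per month; mean = 7.51 − 6 × 0.45/0.55 = 2.60 months.

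The rate ratio is 0.1331/0.0594 = 2.24, but the averages differ by 0.22 months. With all agencies counted, mean time without agreement up to 6 months is p/λ = 5.05 against 4.13 months, a difference of 0.91. With T = 12 the averages among agreeing agencies are 5.64 and 5.21 months.

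The order can also reverse. Suppose arm 2 keeps arm 1's 30% agreeing at a mean of 2.0 months and adds 25% at a mean of 4.5 months. Its average is (0.30 × 2.0 + 0.25 × 4.5)/0.55 = 3.1 months, so the arm that recruits more agencies, and none of them later, looks slower.

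**The alternative on the same example.** With h = 0.08 and 100 agencies, 8 of 100 agree at contact 1, then 7.36 of the remaining 92 at contact 2, and so on: 8% each time, which is the truth that was put in.

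**The case against.** The strongest reply is that these are descriptive secondary outcomes with no stated test or arm comparison. The contact mean is only an example, the handling of undecided agencies may be set out in a fuller document, and the log would support a better analysis. All of this stands and limits the severity. It does not rescue the dose-response label, which the article itself attaches to a mean tied to agreement.

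It is also fair that the average time among agencies that agree answers a legitimate question: how long enrolment takes for an agency that will enrol. That stands, provided the average is labelled as conditional on agreement.

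Two stronger readings are tempting. A reader might infer that these averages will show fewer contacts going with success. The document does not support that as a certainty. Contact also stops at refusal and when effort looks futile, which can shrink or reverse the pattern, and correspondence leading to an MOU may continue after agreement in principle. Nor does the article state that agreeing and non-agreeing agencies will be compared on contacts.

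A reader might also infer that a real difference between arms would be hidden. The article plans no arm comparison of these averages, and M at 6 and 12 months would show a difference in recruitment directly.

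**Conclusion.** The point holds as a minor one. A contact count whose stopping depends on the response cannot be read as dose-response, whichever way it happens to point. The average time to agreement is nearly insensitive to the rate of agreement: 2.8 against 2.6 months at a 2.2-fold difference in rates. That illustration assumes constant rates, no refusals, and that the plan's 30% and 55% are reached at 6 months, which the article does not say. The refusal chances and the timing scenarios are likewise assumptions. The primary metric, its test and the stated power are unaffected. What suffers is the description of recruitment effort and speed that a feasibility study would carry forward.

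**What to change.** 1. Drop the term dose-response for the contact count. If the count is reported, give it for all contacted agencies by final disposition.
2. Report, by arm and type of contact where numbers allow, the proportion agreeing at the k-th contact among agencies still being contacted. Describe it as yield: a fall at later contacts may reflect which agencies are left, not only what a call achieves.
3. Report the cumulative incidence of agreement, and separately of MOU, by arm. Start the clock at first recruitment correspondence, the origin that the H1 analysis section already uses. Keep every agency in which recruitment was started in the risk set, treat refusal as a competing event, and censor undecided agencies at the end of follow-up. Agencies dropped because effort looked futile should stay in the risk set until then, since the decision to stop is informative.
4. Keep the average time among agreeing agencies if wanted, labelled as conditional on agreement.

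The contact log already holds the data, so the cost is wording and a little analysis. The drawback is imprecision at later contacts. With h = 0.035 and r = 0.30, the number of 60 agencies still in contact at the tenth call is 60 × (0.965 × 0.70)^9, or about 2. Show the number at risk at each contact.
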